## Abstract

This study aims to compare the clinical efficacy of transcutaneous photobiomodulation (PBMT) with an 808 nm infrared laser versus intraoral PBMT with a 660 nm red laser in the prevention of oral mucositis (OM). The study is designed to assess whether the transcutaneous approach is non-inferior to the intraoral standard, thereby contributing to the optimization and standardization of PBMT protocols in head and neck cancer (HNC) supportive care. Methods: A randomized pilot study is being conducted with 54 patients (*n* = 27 per group) undergoing radiotherapy (60–70 Gy) for HNC. Participants will be randomly assigned to receive either intraoral PBMT (660 nm, 100 mW, 1 J/point, fluence = 10.20 J/ cm², 10 s, 44 points) or transcutaneous PBMT (808 nm, 100 mW, 1 J/point, fluence = 34.5 J/ cm² (central) and 4.3 J/ cm² (lateral), 10 s, 32 points). Interventions occur three times weekly throughout treatment. The primary outcome is OM severity, graded by WHO scale. Secondary outcomes include OM severity (NCI-CTCAE), pain intensity (Numeric Rating Scale, NRS), ulcerated area extension, registered through digital images, treatment interruptions and unscheduled healthcare utilization. Expected outcomes: the primary hypothesis posits that transcutaneous infrared PBMT is as effective as intraoral red PBMT in mitigating OM severity. Additionally, the transcutaneous approach is expected to offer logistical advantages, including a reduction in application time (80 s vs. 440 s) and improved tolerability in patients with radiation-induced trismus or severe oral pain. Conclusion: This protocol is expected to provide robust evidence to support the most feasible and effective PBMT modality for OM prevention. By optimizing treatment delivery, the study may enhance adherence, preserve nutritional status, and improve the quality of life for patients undergoing oncological therapy.

## Introduction

Head and neck cancer (HNC) encompasses a broad category of various tumor types; approximately 40% of these occur in the oral cavity, 15% in the pharynx, 25% in the larynx, and 20% in other anatomical locations [1, 2]. According to GLOBOCAN data, it is estimated that more than 1.2 million new cases of head and neck cancer will be diagnosed worldwide by 2040 [3].

Antineoplastic treatment (AT) for patients with HNC includes surgical techniques, chemotherapy (CT), radiation therapy (RT), or combination therapy, administered according to the tumor stage and location [4, 5]. For patients with early-stage squamous cell carcinoma, both surgery and radiation therapy yield comparable results in terms of local disease control and overall survival. Following surgery, postoperative radiotherapy, with or without adjuvant chemotherapy, is recommended for patients with pathological risk factors, including perineural invasion, lymphovascular invasion, and positive or narrowly clear surgical margins [6]. RT is an important therapeutic modality for the treatment and control of HNC, as it allows for tumor eradication while preserving the function of normal tissues in the affected region [7], and is used as part of a curative treatment regimen for 75% of patients with head and neck squamous cell carcinoma (HNSCC) [8].

The total radiation dose for curative-intent treatment depends on tumor location and type, typically ranging from 50 to 70 Gy in conventional radiotherapy regimens. In most cases, this dose is delivered in fractions of 1.8 to 2.0 Gy per day, five days a week, over a period of five to seven weeks [9].

Side effects may occur with these treatments; in the oral cavity, the acute effects of RT include oral mucositis, changes in saliva viscosity and volume, dysgeusia, candidiasis, and limited mobility [5]. Chronic effects include neuropathy, atrophy of the facial muscles and salivary glands, halitosis, dysphagia, dysphonia, osteoradionecrosis, xerostomia, hyposalivation, dental caries, and periodontal disease [5].

Oral mucositis (OM) is the most common and challenging complication of radiation therapy or chemoradiotherapy (CRT) in patients undergoing cancer treatment, most commonly found in nearly 100% of patients undergoing high-dose chemotherapy and hematopoietic stem cell transplantation and in 75% to 90% of patients treated for head and neck malignancies [10, 11, 12, 13, 14]. Complications such as painful mouth ulcers and difficulty eating or swallowing are characteristic of OM. The pain and severe dysphagia resulting from OM can lead to significant weight loss in the patient, with a general worsening of their overall condition, and often cause temporary interruption of radiation therapy, which has been shown to reduce its efficacy [14, 15].

In this context, photobiomodulation therapy (PBMT), also known as low-level laser therapy, has emerged as an important adjunctive tool in the prevention and management of OM [16, 17]. PBMT uses light in the red and near-infrared wavelength ranges to modulate cellular processes without causing thermal damage to tissues. The light is absorbed primarily by mitochondrial cytochrome c oxidase and light-sensitive ion channels, triggering increased ATP production, controlled release of reactive oxygen species and nitric oxide, as well as modulation of intracellular calcium [18, 19, 20]. These events activate transcription factors related to cell survival, proliferation, migration, and the synthesis of new proteins, resulting in anti-inflammatory, analgesic, and tissue repair effects [18, 19, 20, 21, 22]. In contexts of oxidative stress, such as during RT, PBMT tends to reduce oxidative stress and inflammation, while simultaneously stimulating mucosal regeneration [19, 21, 22].

In the management of mucositis induced by anticancer therapy, PBMT is used for both preventive and curative purposes, following protocols recommended by international guidelines such as Multinational Association of Supportive Care in Cancer/International Society of Oral Oncology (MASCC/ISOO), particularly in patients undergoing RT and CRT of the head and neck [16, 17, 21]. Preventively, intraoral or transcutaneous application is initiated at the start of treatment and performed regularly (usually daily or several times a week), reducing the incidence, severity, and duration of mucositis, as well as pain intensity and the need for opioids [16, 17, 21, 22, 23]. When lesions are already established, PBMT accelerates healing, shortens the duration of severe mucositis, and improves swallowing, nutrition, and quality of life [16, 22, 24].

Therefore, although there are already clinical trials comparing intraoral and transcutaneous photobiomodulation protocols for the prevention and management of OM in different oncological settings, these studies use heterogeneous parameters and application frequencies, which still hinder the establishment of a standardized protocol for head and neck cancer. Thus, a critical unmet need remains in determining the optimal PBMT delivery strategy—namely, whether intraoral red laser or transcutaneous infrared laser is more appropriate for the prevention and mitigation of radiotherapy-induced OM. Notably, direct comparative evidence between these approaches remains lacking. This randomized study aims to compare the efficacy of these two modalities in patients with head and neck cancer, providing evidence to support the standardization of PBMT protocols and to optimize supportive care during anticancer treatment.

The primary objective of this study is to compare the clinical efficacy of two PBMT protocols: TC PBMT using an 808 nm infrared laser and IO PBMT using a 660 nm red laser for the prevention of OM.

## Materials and methods

### Study Design and Setting 

This pilot study, conducted at a reference oncology center in Paraná, Brazil, compares two distinct PBMT protocols used clinically to prevent OM in patients undergoing radiotherapy for head and neck cancer: TC PBMT (infrared laser) versus IO PBMT (red laser). The two protocols differ in wavelength, fluence, energy per session, number of irradiation points, and application geometry, reflecting the intrinsic characteristics of each available clinical modality. The study aims to compare the overall clinical performance of each protocol. The protocol follows Standard Protocol Items for Recommendations for Interventional Trials (SPIRIT) guidelines. Participants are randomly allocated into one of two intervention: the TC group or the IO group.

### Ethical considerations and registration

The study was approved in October 2024 by the Human Research Ethics Committee of Hospital Erasto Gaertner, under registration number 7.072.369. This study was registered in the Brazilian Registry of Clinical Trials (ensaiosclinicos.gov.br) in June 2025, under registration number RBR-9brv7dd. The participants are informed that they can withdraw from the study at any time for any reason, if they desire.

## Sample size

The sample size was determined based on a non-inferiority design, assuming that transcutaneous infrared PBMT would demonstrate clinical efficacy comparable to intraoral red PBMT in the prevention of OM. The non-inferiority margin was defined as Δ = 0.5 points on the WHO scale, based on the differences observed between CT and IO protocols in direct comparative studies [25, 26]. Calculations were performed using the ClinCalc platform to compare two independent means, assuming a significance level (α) of 0.025 (one-tailed test) and a statistical power (1 - β) of 80%. To account for a predicted 10% attrition rate (dropouts), the final sample size was established at 54 participants (*n* = 27 per group). Participants will be recruited through consecutive sampling to ensure a representative flow of patients at the study site.

## Randomization and blinding

Participants will be randomized (1:1) to TC or IO groups via Random.org (*n* = 54). The research team will perform sequential, simple randomization without blocks or stratification. Due to the distinct application methods and wavelengths (red vs. infrared), double-blinding is unfeasible. Moreover, outcome assessors responsible for WHO and NCI-CTCAE oral mucositis grading cannot be blinded, as the clinical team involved in treatment delivery will also perform the evaluations. Therefore, this is an open-label trial, and the lack of blinding represents a potential limitation of the study. To minimize potential detection bias, examiners will undergo calibration before study initiation, standardized assessment criteria will be applied, and photographic documentation will support mucositis evaluation.

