### Intraoral PBMT

IO PBMT will be administered using the Therapy EC device (DMC^®^, São Carlos, SP, Brazil). This system utilizes an Aluminum Gallium Indium Phosphide (AlGaInP) semiconductor diode laser featuring a single-emitter laser (0.098 cm²). The procedure will be performed in contact mode using a visible red wavelength of 660 nm.

The device operates at an output power of 100 mW, resulting in an irradiance of 1.02 W/cm². Each application point will receive 1 J of energy over a 10-second irradiation interval, corresponding to a fluence of 10.20 J/cm² (Table 1).

Application Technique: A 44-point protocol covers the buccal mucosa [29]. The anatomical distribution is defined as follows:

Buccal mucosa: 16 points (8/ side).Labial mucosa: 8 points (4 superior and 4 inferior).Buccal folds: 6 points (3/ side).Tongue: 9 points (4 on each lateral border and 1 on the tip).Soft palate: 3 points.Labial commissures: 2 points (1/ side).

Total energy is 44 J/ session, lasting 440 s (7 min and 20 s). The clinical mapping of these points is illustrated in Fig. 3.

Three calibrated examiners will perform all clinical assessments; however, blinding will not be feasible in this study due to the visually distinguishable nature of the two PBMT protocols.

For both TC and IO protocols, PBMT will not be applied directly to the gross tumor volume (GTV), as defined in the IMRT planning records available in the patient’s medical record. In cases where any predetermined application point coincides with the GTV, the point will be repositioned or omitted, and this decision will be recorded on the data collection form.

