The examiner will record specific sub-sites and lesion surface area, enabling comparative analysis of TC versus IO PBMT efficacy in reaching anatomically shielded regions, such as the oropharynx and tongue base. The ulcerated area will be quantified through topographic mapping, estimation of the lesion’s extent in cm² using a clinical ruler, and standardized digital intraoral photography.

3.) Pain

The Numerical Rating Scale (NRS) for pain consists of an 11-point scale ranging from 0 to 10, where 0 represents “no pain/difficulty” and 10 indicates the “worst pain/difficulty imaginable.” Patients are asked to choose a whole number that best describes the intensity of the pain or difficulty they are experiencing, facilitating a quick and objective quantification of the painful experience [32].

Assessments will be conducted at baseline, immediately following each PBMT session, and during all subsequent follow-up visits. This longitudinal monitoring aims to evaluate the patient’s symptomatic response to the intervention over time. Participants will be instructed to mark the point on the scale that most accurately represents their current status for each evaluated parameter, providing a quantitative measure of subjective treatment impact.

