### Primary outcome

The primary outcome is OM severity, graded via the WHO scale [ 31], comparing TC versus IO PBMT groups in patients undergoing RT or CRT. Comparative analyses will be performed between transcutaneous and intraoral PBMT groups.

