### Expected results

This study generates comparative data on TC (infrared) versus IO (red) PBMT efficacy for OM prevention during head and neck radiotherapy.

The primary hypothesis is that TC PBMT is non-inferior or superior to IO PBMT in preventing OM. Furthermore, TC PBMT improves compliance in patients with trismus or limited mouth opening, as it obviates the need for prolonged intraoral access during treatment.

Regarding the outcomes of pain and ulcerated area extent, transcutaneous PBMT is expected to demonstrate efficacy equivalent to or superior to that of intraoral PBMT, providing significant relief of pain symptoms through its greater tissue penetration depth and modulation of inflammation.

Furthermore, the results support the development of standardized, evidence-based protocols for the implementation of PBMT in clinical settings, ensuring the consistent and reliable application of this therapy across various patient subgroups. Consequently, this research will provide baseline data for future proposals, serving as a foundation for larger-scale multicenter trials and longitudinal evaluations of the efficacy and safety of photobiomodulation.

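### Neither stated reason makes masked outcome reading impossible, and the planned intraoral photographs would allow it cheaply

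*Protocol article*

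**What the plan says.** All references are to the protocol article.

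- **Randomization and blinding** states that WHO and NCI-CTCAE "grading cannot be blinded, as the clinical team involved in treatment delivery will also perform the evaluations". It discloses that "this is an open-label trial, and the lack of blinding represents a potential limitation of the study". Against detection bias it lists examiner calibration, standardised criteria and photographs: "photographic documentation will support mucositis evaluation".
- **Intraoral PBMT** states "Three calibrated examiners will perform all clinical assessments", and adds that "blinding will not be feasible in this study due to the visually distinguishable nature of the two PBMT protocols".
- **Primary outcome**: "The primary outcome is OM severity, graded via the WHO scale".
- **Data collection** quantifies the ulcerated area by mapping, "estimation of the lesion’s extent in cm² using a clinical ruler, and standardized digital intraoral photography". **Secondary outcomes** links the digital images to ulcerated area at grades 2 to 4.

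Nowhere does the article provide for anyone unaware of allocation to read the photographs.

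**The concern.** The article presents unmasked grading as unavoidable, but its reasons show only that live grading by the treating team is unmasked. A reader or ethics committee would conclude that no masked reading of the outcome can be obtained, although the photographs needed for one are already planned.

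The WHO grade combines signs that an examiner judges (erythema, ulceration) with oral intake. In an open-label non-inferiority trial, a systematic difference in how the arms are graded passes straight into the estimated treatment effect. Depending on its direction, it can produce a false non-inferiority claim or hide a true one. Calibration and common criteria make examiners agree better with one another. They do not stop examiners who all know the arm from leaning the same way. Photographs that support an unmasked grading have the same limit.

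**Working it through.** **Step 1. Test each reason against what it has to show.**

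| Stated reason | What it establishes | Does it rule out masked reading? |
|---|---|---|
| The delivering team also evaluates (Randomization and blinding) | Live graders will know the arm under the chosen staffing | No. It follows from who was assigned to grade |
| The two protocols look different (Intraoral PBMT) | Patients and operators cannot be masked while the laser is applied | No. The difference is seen during irradiation, not by someone reading a coded image later |

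**Step 2. What is already planned.** There are three calibrated examiners, standardised intraoral photography, lesion mapping and ruler measurement. Masked photo reading adds coding, shuffling and reading time, but no new kind of staff or procedure.

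**Step 3. What a photograph can and cannot grade.** In Table 2, WHO 0, 1 and 2 or more differ by normal mucosa, erythema and ulcer, which can be judged on an image. WHO 2, 3 and 4 all have an ulcer and differ only by diet or oral intake, which cannot. Masked reading can therefore support ulcer area and a check on WHO grade 2 or more, not the full scale.

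**Step 4. Illustration of sensitivity to a grading shift.** The article gives no SD and no size for any bias, so both are assumed. From Sample size: margin 0.5, one-sided alpha 0.025, power 80%, 27 per group with 10% attrition. Taking 24 evaluable per arm (24/0.9 = 26.7, rounded up to 27) and no true difference, the implied SD is 0.5/(1.960 + 0.842) × √(24/2) ≈ 0.62. An SD of 1.0 is shown as a second case. The illustration uses a comparison of two means, as the sample size does, not the planned ordinal model.

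With SE = SD × √(2/24) and a grading shift of b grades:
- Error at a true difference of 0.5, shift favouring transcutaneous: Φ(b/SE − 1.96).
- Power at no true difference, shift favouring intraoral: Φ((0.5 − b)/SE − 1.96).

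| SD | SE | b | Error at the margin, shift favours transcutaneous | Power, shift favours intraoral |
|---|---|---|---|---|
| 0.62 | 0.179 | 0 | 0.025 | 0.80 |
| 0.62 | 0.179 | 0.1 | 0.08 | 0.61 |
| 0.62 | 0.179 | 0.2 | 0.20 | 0.39 |
| 1.0 | 0.289 | 0 | 0.025 | 0.41 |
| 1.0 | 0.289 | 0.1 | 0.05 | 0.28 |
| 1.0 | 0.289 | 0.2 | 0.10 | 0.18 |

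Shifts well inside the 0.5 margin would matter in either direction. The table does not say that such a shift will occur.

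**Step 5. Reading load.** Thirty to 35 fractions at five a week is 6 to 7 weeks. Three sessions a week gives 18 to 21 visits per participant, and for 54 participants 972 to 1,134 visits. If every visit were photographed, reading would take about 16 to 19 hours at an assumed one minute per visit, and 32 to 38 hours at two.

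**The case against.** The strongest reply is that this is a single-centre pilot that openly calls itself open-label, names the lack of blinding as a limitation and lists three countermeasures, one of them photographic. No figure is wrong. That is fair: nothing is concealed and the disclosure should stay. Disclosure does not make the claim of impossibility correct, however, and the photographic countermeasure as described is not masked.

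Some stronger readings that a reader might infer are not supported:

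- **That the clinician who treats a participant also grades that participant.** The article speaks of the delivering team and of three examiners. It does not say who grades whom.
- **That the bias favours transcutaneous treatment.** Expected results says "The primary hypothesis is that TC PBMT is non-inferior or superior to IO PBMT in preventing OM". But the Discussion calls the intraoral route the current clinical standard and credits it with delivering light directly to the target mucosa. Expectation could run either way.
- **That the two sections contradict each other.** Randomization and blinding itself mentions both the different application methods and the team's double role, so the reasons are complementary. Each falls short of what it is used to show.
- **That photographs exist for every visit.** This is not clearly stated, and Secondary outcomes ties images to grades 2 to 4. If images were taken only after an unmasked diagnosis of ulceration, re-reading could not recover lesions that were under-called.
- **That masked live grading needs only a change of rota.** No section says that any examiner is free of treatment delivery, and Clinical and treatment-related variables cites researcher availability as a constraint, although for session frequency.

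**Conclusion.** The point holds in a limited form. The reasons given justify saying that patients and operators cannot be masked and that live grading will be unmasked as staffed. They do not justify saying that masked reading of the outcome is impossible. The planned photographs could supply one at modest cost for ulcer area, and for a check on the ulcer threshold of the primary outcome.

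The bias at stake cannot be sized or signed from the document. The error rates and power in the illustration rest on an assumed SD, 24 evaluable per arm and assumed shifts of 0.1 and 0.2 grade. The conclusion itself rests on the article's two stated reasons and its planned resources, not on those figures.

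Two limits remain after the fix. Masked reading cannot verify the distinction between WHO grades 2, 3 and 4. It also comes after the event, so it does not change the fact that an unmasked diagnosis of ulcerative mucositis starts therapeutic irradiation (Standard supportive care protocol). This is an inexpensive improvement to the design, not a fault that invalidates it.

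**What to change.** 1. State that intraoral photographs are taken on the same schedule in both arms, whether or not an ulcer has been diagnosed.
2. Code and shuffle the images. Have one of the three existing examiners, who did not treat that participant, re-read them without allocation for no lesion, erythema, ulcer and ulcer area.
3. Use the masked readings for the ulcer-area outcome and for a sensitivity analysis of WHO grade 2 or more.
4. Where the rota allows, have an examiner who does not deliver that participant's PBMT do the live grading before the session.
5. Keep the open-label disclosure. Reword Randomization and blinding and Intraoral PBMT to say that live grading is unmasked for staffing reasons, rather than that blinding is impossible.

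The cost is coding and reading time for existing staff, possibly tens of hours if every visit is photographed and less on a sparser common schedule. Masking will be imperfect: a reader from a small team may recognise a participant, and at live grading participants may reveal their arm.
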